## Abstract

**Background:**

Underage drinking is a prevalent risk behavior and common public health problem. Research shows that alcohol abuse not only affects the quality of life of drinkers themselves. The problems resulting from underage drinking pose substantial costs to society as well. The proposed study will address underage drinking with the use of an Internet campaign, which is a cost-effective way of tackling the problem.

**Objective:**

The aims of this study are to test the effectiveness of an online quiz competition in changing adolescents’ alcohol-related attitudes and behavior and to explore the feasibility of using Internet viral marketing to reach a significant number of adolescents.

**Methods:**

The study will constitute a cluster randomized controlled trial for 20 secondary schools (6720 Grade 7-9 students). Schools will be randomized to intervention or control arm with equal likelihood. Students in intervention schools will be invited to take part in the Internet campaign, whereas those in control schools will receive relevant promotional leaflets.

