## Methods

### Study Design

The proposed study will consist of a cluster randomized controlled trial on the effectiveness of an Internet quiz competition in promoting healthy attitudes and behaviors towards alcohol use among adolescents. As the intervention website could be referred by participants, cluster randomization, instead of individual-level randomization, is chosen to minimize treatment contamination. The study will employ an Internet viral marketing strategy to maximize sample size. In total, 24 schools (6552 Grade 7-9 students) will be recruited with the collaboration of our community partners such as the Tung Wah Group of Hospitals. Considering that the average number of students in one secondary school class is 35 and that there are four classes in each grade, a total of 10,080 students (24×3×4×35) will be reached. Assuming a response rate of 65%, the number of effective campaign starters will be 6552. Students who cannot comprehend basic Chinese and Cantonese will be excluded.

Half the schools will be randomized for the Internet quiz competition campaign (intervention arm) and half will be randomized for an information package (control arm). Students in the intervention group will be given the opportunity to take part in the online quiz competition and refer others to join the campaign, whereas those in the control group will receive an electronic information package containing comparable information as the intervention arm. All participating students’ demographics and change in attitude and behavior will be measured by questionnaire surveys before intervention, within 1 month, and between 2-3 months after intervention. A longer-term follow-up (12 months after intervention) will also be attempted if schools are willing to commit and resources allow. Weblog data will also be collected from website servers for subsequent analysis of the effectiveness of the Internet viral marketing strategy. Figure 1 is a flowchart of the proposed study.

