### Power Analysis

Considering an attitude difference in 50% of the pooled standard deviation (SD) to be minimally satisfactory, we will need a sample size of 128 to examine, via a two-sample independent *t* test, whether the campaign is more effective than a traditional promotion strategy at a .05 significance level and 80% power [19]. Due to our cluster study design, intraclass correlation (ICC) needs to be addressed. It was reported that an ICC of attitude-related construct among schools was about 0.092 [20], which inflates the required sample size to N=n×[1+(K‒1)×ICC]=128×[1+(3×4×35‒1)×0.092]≈5063. Hence, the number of starters to be recruited (6552) will be sufficient to achieve the study’s primary aim regardless of the number of referrals.

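### The abstract gives the trial as 20 schools and 6720 students, the Methods as 24 schools and 6552; power is adequate either way, but the number of randomized schools must be stated once

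*Protocol article*

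**What the plan says.** The Methods paragraph of the abstract gives the size as "The study will constitute a cluster randomized controlled trial for 20 secondary schools (6720 Grade 7-9 students"), and adds: "Schools will be randomized to intervention or control arm with equal likelihood". It states no response rate and no students-per-school figure.

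Study Design gives a different size: "In total, 24 schools (6552 Grade 7-9 students) will be recruited". It shows how this was obtained. Three grades, four classes per grade and 35 students per class mean that "a total of 10,080 students (24×3×4×35) will be reached". Then: "Assuming a response rate of 65%, the number of effective campaign starters will be 6552". Half the schools go to each arm, so 12 and 12.

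Power Analysis works from a difference of 0.5 SD, 80% power and an ICC of 0.092, reaches a requirement of about 5063 students, and concludes that "the number of starters to be recruited (6552) will be sufficient to achieve" the primary aim. It does not mention 6720 or 20 schools.

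**The concern.** Both the number of randomized units and the number of students differ, and they differ in opposite directions: the abstract has four fewer schools and 168 more students. Both statements are current text about the same planned trial, and no amendment or explanatory sentence links them.

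The number of schools is the recruitment target of a cluster trial and, at an ICC of 0.092, the main determinant of its precision. While two numbers stand, a 20-school trial could be reported as having met its target or as having fallen four schools short, depending on which sentence is cited. A reader who goes by the abstract's student total would also take that version for the larger trial, when it carries less information.

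**Working it through.** **Inputs.** From Study Design: 24 schools, 3 × 4 × 35 = 420 students per school, 65% response. From the abstract: 20 schools, 6720 students, 1:1 allocation. From Power Analysis: difference 0.5 SD, alpha 0.05, 80% power, unadjusted total 128, ICC 0.092. Assumed because the article does not state them: two-sided alpha and equal school sizes.

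**1. Reproduce the plan's figures.**
- Enrolment: 24 × 420 = 10,080; 10,080 × 0.65 = 6552. Exact.
- Unadjusted size: the exact t calculation with 64 per arm gives 80.1% power, so 128 reproduces.
- Inflated size: 128 × [1 + (420 − 1) × 0.092] = 5062.1, which rounds up to the stated 5063.

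**2. Can one slip explain the abstract?**
- 20 × 420 = 8400, and 6720 / 8400 = 80% exactly. This borrows the 420 per school from Study Design.
- At the stated 65%, 20 schools give 8400 × 0.65 = 5460, not 6720.
- At 65%, 6720 students would need 6720 / (0.65 × 420) = 24.6 schools.

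Changing only the school count, or only the response rate, does not turn one version into the other.

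**3. Precision under each version.** Design effect DE = 1 + (m − 1) × 0.092, with m the enrolled students per school. Effective n = N / DE. SE of the difference in SD units = √(4 / effective n). Power for 0.5 SD comes from the noncentral t with noncentrality 0.5 / SE on (schools − 2) degrees of freedom. The difference detectable with 80% power is approximately (t0.975 + t0.80) × SE.

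| Version | m | DE | Effective n | SE | Power for 0.5 SD | Detectable difference, 80% power |
|---|---|---|---|---|---|---|
| 24 schools, 6552 | 273 | 1 + 272 × 0.092 = 26.02 | 251.8 | 0.126 | 96.6% | 0.37 SD |
| 20 schools, 6720 | 336 | 1 + 335 × 0.092 = 31.82 | 211.2 | 0.138 | 93.0% | 0.41 SD |
| 20 schools at 65%, 5460 | 273 | 26.02 | 209.8 | 0.138 | 92.8% | 0.41 SD |

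With the normal approximation instead of t, the first two rows give 97.8% and 95.3% power, and detectable differences of 0.35 and 0.39 SD.

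**4. Compare.** Effective sample: 211.2 / 251.8 = 0.84, so about 16% less with 20 schools. The last two rows show why: with 20 schools, dropping from 6720 to 5460 students changes effective n only from 211 to 210, whereas going from 24 to 20 schools costs about 40.

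Against the plan's own requirement of 5063, the margins are 6552 / 5063 = 1.29, 6720 / 5063 = 1.33 and 5460 / 5063 = 1.08. All three pass.

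**The case against.** The strongest reply is that nothing of substance depends on the difference. Every version exceeds 5063 students and has more than 90% power for 0.5 SD, against a planned 80%; the detectable difference moves from 0.37 to 0.41 SD, still below the target. This stands. A reader might infer that the abstract's trial is underpowered, and the plan's own inputs do not support that.

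A second reply is that the Methods are internally consistent: the size is derived in full and 6552 is carried into the power statement, while the abstract has one sentence without derivation. This also stands in large part. A reader might infer two rival designs of equal standing. The more natural reading is an abstract not matched to the body, although the article does not prove it.

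A third reply concerns the 80%. A reader might infer that the sponsor planned on two response rates. Only 65% is documented; 80% is obtained by applying the Methods' school structure to the abstract's totals. The match is exact and therefore plausible, but it remains an inference. Nor does the article say that only 20 schools were in fact recruited.

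What survives all three replies is that the article gives two different numbers of randomized schools and does not say which is the target.

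**Conclusion.** The inconsistency is real and explicit: 20 schools and 6720 students in the abstract, 24 schools and 6552 students in Study Design and, for the student total, in Power Analysis. It is a moderate reporting inconsistency in a key design figure and does not threaten the conclusion that the trial is large enough. Power for 0.5 SD is about 97% with 24 schools and about 93% with 20; the abstract's version has about 16% less effective sample despite its 168 extra students.

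These sizes rest on the plan's ICC of 0.092, equal school sizes, two-sided 0.05 and t on schools − 2 degrees of freedom. The second decimal of the detectable differences depends on that choice of method. The existence of the contradiction depends on none of these assumptions.

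**What to change.** State one number of schools, one response rate and one student total in the abstract, Study Design and Power Analysis.

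- **If 24 schools is the target**, as the complete derivation suggests, correct the abstract to 24 schools (12 per arm) and 6552 students at 65% response. Nothing else changes.
- **If 20 schools is the target**, rewrite Study Design and Power Analysis with 20 schools (10 per arm) and the response rate actually assumed. At 65% this is 5460 students, still above 5063. Restate the power as about 93% for 0.5 SD, with 80% power at about 0.41 SD. If a rate of 80% was meant, say so and justify it.

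The first route costs one sentence. The second costs a short recalculation and a slightly less favourable stated precision. Neither alters the design.

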**Results:**

Alcohol-related attitude and behavior will be the primary outcome measures. The results of the proposed study will provide evidence on the efficacy of an Internet intervention in modifying adolescents’ attitudes and behavior and guide further investigation into the prevention of and intervention in such risk behaviors as underage drinking. The project was funded July 2015, enrollment started September 2015, and results are expected July 2017.

**Conclusions:**

With the Internet increasingly being recognized as a practical and cost-effective platform for health information delivery, the proposed Internet-based intervention is expected to be more effective in altering adolescents’ alcohol-related attitudes and behaviors than traditional health promotion.

**ClinicalTrial:**

ClinicalTrials.gov NCT02450344; https://clinicaltrials.gov/ct2/show/NCT02450344 (Archived by WebCite at http://www.webcitation.org/6heB2zMBD)

## Introduction

### Background

Underage drinking is a leading global public health problem. Each year, many underage drinkers die from motor vehicle crashes, homicide, suicide, falls, burns­, and drowning [1]. Research shows that alcohol abuse not only affects the quality of life of drinkers themselves; the problems resulting from underage drinking pose substantial costs to society as well [2]. The proposed study will address underage drinking because, like many other behaviors that pose a health risk such as cigarette smoking and unprotected sex, excessive alcohol consumption habits acquired during adolescence can be tracked into adulthood, thereby harming both current health and health later in life [3]. Studies on the long-term health impacts attributable to alcohol use have found adolescents who start drinking at an early age are more likely to binge drink during adulthood [4]. Moreover, young people’s susceptibility to peer influence peaks during the middle adolescent years, which renders that age group particularly vulnerable to underage alcohol use [5]. In light of these associations and risks, it is recommended that alcohol-related interventions and prevention strategies be initiated as early as during adolescence to obtain maximal benefits.

### Underage Drinking and its Prevalence

Adolescence is a period of stress, during which feelings of insecurity are high and motivation is low [6]. Traditional intervention means may be inadequate to engage youths. As adolescents have been found more open than other age groups to the new possibilities offered by the Internet [7], this medium provides an innovative platform for an intervention program targeting this population. Viral marketing through the peer dissemination of information online may be particularly applicable to changing adolescents’ perceptions and engagement in risk behaviors. The aim of the proposed study is therefore to investigate the extent to which an Internet viral marketing campaign can change drinking behavior and attitudes towards alcohol use among Chinese adolescents.

Underage drinking poses a multitude of risks for teens, their families, and society as a whole, and the prevalence of underage drinking among today’s adolescents is widespread internationally [8]. In 2011, for example, the US National Survey on Drug Use and Health reported that 25% of American youths aged 12-20 drink alcohol, with 16% reporting binge drinking [9]. In Korea, a study of 2124 students attending junior and high schools in Seoul showed that 68% of those aged 12-16 were monthly drinkers and that 28% drank alcohol weekly [10].

The situation in Hong Kong is equally worrying, with the Child Health Survey of 2005/2006 reporting that a significant proportion of children aged 11-14 were current binge drinkers [11]. A more recent survey conducted by the Narcotics Division in 2008 showed that 64.9% of secondary school students had consumed alcohol at least once [12]. The abolition of beer and wine taxes in 2008 and subsequent fierce advertising by the alcohol industry and open endorsement of alcohol by top government officials have further aggravated the local underage drinking problem. School surveys have found a significant increase in monthly alcohol drinking in both adolescent boys (from 19.1% in 2006/7 to 30.4% in 2009/10) and girls (from 16.5% in 2006/7 to 27.5% in 2009/10) after the alcohol tax cut [13]. Hence, there is a pressing need for alcohol-related interventions to stop the growing trend of underage drinking in Hong Kong.

### Transition From Traditional to Internet-Based Alcohol Interventions

Although traditional alcohol interventions by mail or health talks delivered by health care professionals have demonstrated efficacy, it remains difficult to engage adolescents with underage drinking problems who are unwilling or simply do not seek assistance through traditional health services or self-help groups. The Internet, because of its increasing usage among today’s youth, can be an effective medium to engage this high-risk population. There is evidence to support the benefit of online alcohol intervention to reach groups less likely to access traditional alcohol-related services, such as young people, and the evidence also supports its potential to effect behavioral change in large numbers of people [14].

### Internet Viral Marketing and its Efficacy

Internet viral marketing, or the electronic “word-of-mouth” dissemination of information, is one of the best-recognized forms of Internet-based marketing. Research shows that viral marketing is a more effective and efficient marketing tool than traditional media, and one that is characterized by its low cost and exponential transmission of information [15]. A recent prospective pilot study conducted by Ip and [name] assessed the efficacy of an online game-based viral marketing campaign in promoting antismoking attitudes among Chinese adolescents. During the 22-day campaign, the study observed an eightfold increase in the number of participants and a significant attitudinal change, with 73% holding a negative attitude towards smoking after the campaign compared to 57% before it [16]. These promising results suggest the potential effectiveness of adopting a similar viral marketing model to engage youth and promulgate alcohol-related health information among Chinese adolescents.

### Attitudinal Change and its Effects on Behavior

The theory of reasoned action and theory of planned behavior are the most frequently tested models of attitude-behavior relations. Both models view a particular behavior as a function of salient information, or beliefs, relevant to that behavior [17]. Beliefs about the positive outcomes of a behavior lead people to favor and engage in that behavior, while beliefs about its undesirable consequences hinder them from doing so. Research also supports the correlation between attitudinal change and behavioral change [18]. Hence, interventions aimed at changing attitudes towards alcohol use have the potential to induce simultaneous changes in drinking behavior. The aims of this study are to test the effectiveness of an online quiz competition in changing adolescents’ alcohol-related attitudes and behavior and to explore the feasibility of using Internet viral marketing to reach a significant number of adolescents.

## Methods

### Study Design

The proposed study will consist of a cluster randomized controlled trial on the effectiveness of an Internet quiz competition in promoting healthy attitudes and behaviors towards alcohol use among adolescents. As the intervention website could be referred by participants, cluster randomization, instead of individual-level randomization, is chosen to minimize treatment contamination. The study will employ an Internet viral marketing strategy to maximize sample size. In total, 24 schools (6552 Grade 7-9 students) will be recruited with the collaboration of our community partners such as the Tung Wah Group of Hospitals. Considering that the average number of students in one secondary school class is 35 and that there are four classes in each grade, a total of 10,080 students (24×3×4×35) will be reached. Assuming a response rate of 65%, the number of effective campaign starters will be 6552. Students who cannot comprehend basic Chinese and Cantonese will be excluded.

Half the schools will be randomized for the Internet quiz competition campaign (intervention arm) and half will be randomized for an information package (control arm). Students in the intervention group will be given the opportunity to take part in the online quiz competition and refer others to join the campaign, whereas those in the control group will receive an electronic information package containing comparable information as the intervention arm. All participating students’ demographics and change in attitude and behavior will be measured by questionnaire surveys before intervention, within 1 month, and between 2-3 months after intervention. A longer-term follow-up (12 months after intervention) will also be attempted if schools are willing to commit and resources allow. Weblog data will also be collected from website servers for subsequent analysis of the effectiveness of the Internet viral marketing strategy. Figure 1 is a flowchart of the proposed study.

**Figure 1 figure1:**
[figure not shown]
Flowchart of the research design.

### Power Analysis

Considering an attitude difference in 50% of the pooled standard deviation (SD) to be minimally satisfactory, we will need a sample size of 128 to examine, via a two-sample independent *t* test, whether the campaign is more effective than a traditional promotion strategy at a .05 significance level and 80% power [19]. Due to our cluster study design, intraclass correlation (ICC) needs to be addressed. It was reported that an ICC of attitude-related construct among schools was about 0.092 [20], which inflates the required sample size to N=n×[1+(K‒1)×ICC]=128×[1+(3×4×35‒1)×0.092]≈5063. Hence, the number of starters to be recruited (6552) will be sufficient to achieve the study’s primary aim regardless of the number of referrals.

### Intervention Arm: Internet Quiz Competition Campaign

The intervention is designed based on the Theory of Planned Behavior. Participants will gain alcohol-related knowledge through the participation of the intervention, which would in turn alter their attitude concerning drinking and alcohol use. According to the Theory of Planned Behavior, such knowledge and attitude improvement would reduce participants’ intention to drink and thus change or prevent their drinking behavior [21]. To promote the intervention, we will conduct a briefing session and a demonstration session for all eligible students in participating schools in the intervention arm. Campaign promotion brochures and posters will be distributed within those schools.

### Campaign Design

Participants of the campaign will receive a referral code from those who refer them to the online quiz website; starters of the campaigns will receive the code directly from the research team. These referral codes, sets of 8-digit numbers, will be unique to each user and used to track the referral process. During registration, participants will be asked to provide basic demographic information and their referral code. After registration, their baseline attitudes and behavior will be assessed using the Alcohol Attitudes and Behavior survey.

The campaign will last for 30 days, starting from the day of the school promotion session. The aim of the competition from the participants’ perspective will be to obtain the highest score possible to win a prize. They will have two ways of doing so.

The first way will be to answer the online quiz questions. The po­ints gained in this way will constitute the “answer score.” Alcohol-related multiple-choice questions will be presented on the webpage one by one in random non-repeated order. Each correct answer will result in 10 points being awarded to the user’s account. Giving an incorrect answer or skipping a question will not result in any points being deducted. Users will be shown the correct answer immediately after they have chosen their own. The purpose of this design is to promote correct alcohol-related knowledge and attitudes.

The second way of accruing points to obtain a high score will be to make referrals, a step designed to enhance the effectiveness of the Internet viral marketing strategy. Upon a successful referral, the referrer will receive all of the answer scores of their direct referrals (which will constitute their “referral score”). To minimize the chance of self-referrals, users will receive no points from making a successful referral. Furthermore, to ensure campaign competitiveness, the referral scores of lower-level users will not be added to starters’ accounts. The answer score and referral score will be summed into a total score that will be used for prize distribution. Figure 2 illustrates the point system.

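### Study Design and Campaign Design are not reconciled on when, and in which students, baseline is measured; if Campaign Design governs, the intervention baseline is post-promotion and self-selected

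*Protocol article*

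**What the plan says.** Two parts of the protocol article describe the baseline.

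- **Study Design**, in a paragraph covering both arms, says that participating students' demographics and change in attitude and behaviour "will be measured by questionnaire surveys before intervention, within 1 month, and between 2-3 months after intervention". Quiz entry is presented there as optional: "Students in the intervention group will be given the opportunity to take part in the online quiz competition and refer others to join the campaign".
- **Campaign Design** describes registration on the quiz website, both for referred users and for starters, who get their code directly from the research team. It then says: "After registration, their baseline attitudes and behavior will be assessed using the Alcohol Attitudes and Behavior survey". The survey it names is the one that the outcome sections use for both primary outcomes.

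Three further statements bear on timing and population.

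- Campaign Design: "The campaign will last for 30 days, starting from the day of the school promotion session".
- Intervention Arm: "we will conduct a briefing session and a demonstration session for all eligible students in participating schools in the intervention arm". Brochures and posters are also distributed in those schools. The Control Arm section gives the information package to all control students and mentions neither promotion nor registration.
- Study Design: "Assuming a response rate of 65%, the number of effective campaign starters will be 6552". It also says: "The study will employ an Internet viral marketing strategy to maximize sample size".

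The only explicit restriction on who is analysed is in the Control Arm section: control students who report having joined the quiz are excluded.

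**The concern.** Study Design suggests one pre-intervention survey, the same in both arms. Campaign Design attaches the word baseline to a survey that a student reaches only by registering for a prize competition. A site that followed Campaign Design literally would collect the intervention baseline after allocation is known, on or after promotion day, and only from students who opted in. Nothing in the control arm corresponds to this.

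Two things would then be at stake. Randomising schools does not protect against students entering the comparison by different routes in the two arms after allocation. And if the promotion material itself moves attitudes, a baseline taken after it already contains part of the effect, so change from baseline in that arm would be understated.

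This is a field procedure stated in two ways, not a detail left to an analysis plan. A baseline missed before promotion cannot be collected afterwards.

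**Working it through.** **1. The article's own figures.** The Abstract gives 20 schools and 6720 students; the figures here follow the 24 schools of the Methods.

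- Students reached: 24 × 3 × 4 × 35 = 10,080. At 65% response: 10,080 × 0.65 = 6552. Reproduced.
- Sample size: 0.5 SD, two-sided 0.05 and 80% power need 64 per arm by the t test, so 128. Design effect 1 + (420 − 1) × 0.092 = 39.548; 128 × 39.548 = 5062.1, so 5063. Reproduced.

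**2. Who the starters are.** Each school has 3 × 4 × 35 = 420 eligible students. Half of the 24 schools run the campaign, so intervention schools supply 12 × 420 × 0.65 = 3276 respondents. The other 3276 are in control schools, which have no campaign to start. The 6552 are therefore expected survey respondents in both arms, although Study Design and Power Analysis call them starters.

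**3. The two readings of baseline.**

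| | Separate survey of all participants (Study Design) | Website survey is the baseline (Campaign Design) |
|---|---|---|
| Intervention arm, who | All participating students | Registrants only |
| Intervention arm, when | Before intervention; order relative to promotion not stated | After registration, so on or after promotion day |
| Control arm | Same survey | No registration step; route not described |
| Comparable? | Yes, if given before promotion | Not assured |

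That registration falls on or after promotion day is inferred from the campaign's start day; it is not stated outright. Under the first reading, registrants complete the same survey twice before the quiz, and the article does not say which one counts as baseline.

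**4. Precision.** With 12 schools per arm, ICC 0.092 and 420 × 0.65 = 273 respondents per school, the standard error of the arm difference is √[2 × (0.092 + 0.908/273)/12] = 0.126 SD.

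**5. Illustration of bias, on assumed inputs only.** Suppose a share u of intervention students registers and registrants differ from non-registrants by D SD. The registrant mean then departs from the whole-school mean by (1 − u) × D.

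| u | D (SD) | Shift (SD) | Shift ÷ 0.126 |
|---|---|---|---|
| 0.65 | 0.2 | 0.35 × 0.2 = 0.070 | 0.6 |
| 0.65 | 0.3 | 0.35 × 0.3 = 0.105 | 0.8 |
| 0.50 | 0.5 | 0.50 × 0.5 = 0.250 | 2.0 |

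Neither u nor D is in the document. The 65% is a response rate applied to all 24 schools, and its use for u is an assumption. The shift is the gap between arms only if control respondents represent their whole school.

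**6. Power is not the issue.** With control response at 65%, power for 0.5 SD is 0.973 if 20% of intervention students register and 0.978 if 65% do (normal approximation).

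**The case against.** The strongest reply is that Study Design already settles the matter. It plans a pre-intervention survey of all participating students and makes quiz entry optional, so the trial baseline need not depend on registering. Campaign Design may describe only the website workflow, which also has to cover referred users who can be assessed nowhere else. A survey taken after registration but before the first quiz question could still count as before intervention. The promotion session is there to advertise the quiz, and its alcohol content is not described, so its effect on attitudes is speculative.

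Much of this stands. A reader might infer that baseline exists only for registrants and that only registrants are analysed. The documents do not support that as fact: Study Design points the other way, no analysis population is defined in the article, and a condensed article may leave that definition to a fuller document. Nor does the article put referred outsiders into the arm comparison; Power Analysis says the planned starters suffice whatever the number of referrals.

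The shifts in the illustration are open to the same criticism. They shrink if control respondents are similarly selected, which an equal 65% response would allow. They are also differences in level, and a stable level difference cancels in change scores; bias in change would need registrants to change differently from other students or promotion to move the baseline.

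What the reply does not remove is that Campaign Design applies the word baseline to starters as well as to referred users, names the outcome instrument, and is nowhere described as additional to the Study Design survey.

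**Conclusion.** The point holds as an unreconciled conflict with a conditional consequence. If Campaign Design governs, the intervention baseline is post-allocation, on or after promotion day and self-selected, with no counterpart in the control arm, and levels and change scores may not be comparable. If Study Design governs and its survey precedes promotion, the problem disappears.

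The size of the bias cannot be derived from the document. The shifts of 0.07 to 0.25 SD, against a standard error of 0.126 SD and a target of 0.5 SD, show only that plausible selection could matter; they rest wholly on assumed inputs. The concern is bias, not power. The one firm figure is that about 3276 of the 6552 so-called starters would be in schools that run the campaign.

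**What to change.** Reconcile Study Design and Campaign Design as follows.

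1. State that the same baseline survey is given in all schools of both arms before any briefing, promotion session or information package.
2. State that students who complete it are analysed by their school's allocation, whether or not they register for the quiz.
3. Describe the website survey as additional, for example for referred users.
4. Use referred users from outside the randomised schools only for the reach objective, and amend the sentence that links viral marketing to sample size.
5. In Study Design and Power Analysis, call the 6552 survey respondents and keep the word starters for campaign users in intervention schools.

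The cost is one survey sitting moved earlier and a few sentences of text. Analysing all baseline completers also means that students in intervention schools who never use the quiz dilute the estimated effect.
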